## Abstract

Introduction: Manual material handling (MMH) workers are at an increased risk of work-related musculoskeletal disorders (WMSDs) due to the physically demanding nature of their tasks. Traditional ergonomic training methods often fail to engage learners effectively. This protocol describes an Augmented Reality Physical Ergonomics (ARPE) training module that aims to enhance ergonomic knowledge, supports worker self-assessment, and encourages preventive practices through an immersive, interactive learning experience.

Methods: The ARPE module was developed with a literature review, expert input, and pilot usability testing and is delivered via a mobile XR app featuring 3D task simulations and ergonomic demonstrations. We will conduct a two-arm, six-week quasi-experimental study in manufacturing settings (n=78 MMH workers; 1:1 ARPE vs. standard Department of Occupational Safety and Health (DOSH) training). Outcomes will be measured at baseline, immediately post-training, and at six weeks. The primary outcome is ergonomic knowledge; secondary outcomes are self-prevention behaviors and self-evaluation. Group differences across time will be evaluated using repeated-measures methods. A separate usability assessment of the ARPE app employed a validated mHealth usability questionnaire in an independent worker sample.

Results: As this is a study protocol, results are not yet available. The study is designed to assess changes in ergonomic knowledge (primary outcome) and self-prevention behaviors and self-evaluation (secondary outcomes). Data collection and analysis are planned through November 2025.

Ethics and trial registration: The study was approved by the Research Ethics Committee of Universiti Teknologi MARA (UiTM) (approval number: REC/11/2024 (PG/MR/550)) and is registered with ClinicalTrials.gov (US National Library of Medicine) under the identifier NCT06993298.

Conclusion: This protocol describes an augmented reality (AR)-based ergonomic training module (ARPE) that aims to provide an innovative, expert-validated, immersive approach to training. The study will evaluate effects on ergonomic knowledge (primary), self-prevention behaviors, and self-evaluation among MMH workers. Findings may support the use of AR as a scalable occupational health training tool and may inform strategies to reduce work-related musculoskeletal risk.

## Introduction

Work-related musculoskeletal disorders (WMSDs) are a major cause of occupational health problems and lost productivity worldwide, especially among manual material handling (MMH) workers who regularly lift, lower, push, pull, or carry loads [1-3]. In Malaysia, WMSDs pose significant health and economic challenges, as shown by risk patterns among industrial workers and records of compensation claims [4,5]. Ergonomics training is essential for prevention; however, traditional methods, such as lectures, static videos, and one-way briefings, often lack interactivity, practical application, and immediate feedback. These limitations lead to poorer knowledge retention, limited skill development, and less effective behavior change [6-8].

Augmented reality (AR) in ergonomic learning involves overlaying digital content onto real tasks, enabling workers to visualize risk factors (e.g., awkward postures, load paths), receive instant cues, and practice safer techniques on-site. By combining task-specific guidance with real-time feedback, AR aims to improve understanding, support self-assessment, and promote preventive actions during MMH activities [9-11]. In safety-critical fields such as construction, manufacturing, healthcare, and aviation, AR/virtual reality (VR) training has been shown to increase engagement, procedural accuracy, postural awareness, and knowledge transfer compared to traditional passive methods [7,10,12]. However, comprehensive evaluations focusing on MMH ergonomics in Malaysia aligned with national guidelines and measuring ergonomic knowledge (primary), along with self-preventive behaviors and self-assessment (secondary), using quasi-experimental designs are still limited [4,11,13,14]. On the other hand, studies highlight the positive impact of AR on cognitive skill acquisition, learning transfer, and real-time error correction among workers in physically demanding roles [15]. Workers also report higher engagement levels and motivation to participate in repeated training sessions when AR is used [16]. Thus, this study aims to develop and evaluate an Augmented Reality Physical Ergonomics (ARPE) training module for MMH workers by aligning immersive, task-level content with local ergonomic guidelines, specifically, to design, develop, and content validate the ARPE module; determine its usability among MMH workers; and test its effectiveness in a two-arm intervention (ARPE versus guideline-based control). The primary effectiveness objective is to determine whether ARPE yields a greater increase in ergonomic knowledge from baseline (t_0_) to immediate post-training (t_1_) than guideline-based training, while secondary objectives are to assess whether ARPE improves self-prevention behaviors and self-evaluation at t1 and at six-week follow-up (t_2_). The primary goal is to determine if ARPE leads to a greater increase in ergonomic knowledge from baseline to immediate post-training (t_0_→t_1_) compared to guideline-based training. The secondary goals are to assess whether ARPE improves self-prevention behaviors and self-evaluation at t_1 _and during the six-week follow-up (t_2_). If proven effective, ARPE could complement traditional training and promote safer work practices, although longer-term outcomes (such as WMSD incidence and productivity) are beyond the scope of this protocol.

## Materials and methods

This study used a mixed-methods approach combining both qualitative and quantitative techniques across two main phases. The aim was to develop, validate, and evaluate an ARPE training module for MMH workers. In Phase 1, the focus was on designing and validating the AR content, platform, and assessment tools, followed by usability testing. Phase 2 involved a quasi-experimental intervention to measure the module's impact on ergonomic knowledge, self-prevention behaviors, and self-evaluation skills.

Approval of ethics

This study received approval from the Research Ethics Committee of Universiti Teknologi MARA (UiTM) (approval number: REC/11/2024 (PG/MR/550)). It will be conducted in accordance with the Declaration of Helsinki and the Malaysian Good Clinical Practice Guideline. All participants will receive a study information sheet and provide written informed consent before any procedures. Participant privacy will be protected via deidentification (coded IDs), with direct identifiers stored separately from research data. Electronic files will be maintained on secure, password-protected, access-restricted institutional servers; any hard-copy materials will be kept in locked storage. Only authorized study personnel will have access to identifiable data, and results will be reported in aggregate to minimize re-identification risk. Any substantial protocol amendments will be submitted to the Research Ethics Committee and communicated to relevant stakeholders.

Phase 1a: development and content validation of the ARPE training module

In Phase 1a, the fuzzy Delphi method (FDM) was employed to achieve expert consensus on the content of the AR ergonomic training module. Ten experts were purposively selected from diverse fields, including public health, occupational health, ergonomics, and instructional design in educational technology. This phase involved online interviews to validate training content based on relevant literature and established ergonomic guidelines. Structured rounds of questionnaires using a 7-point Likert scale were administered to refine the content, ensuring methodological rigor and reducing subjectivity [17]. Expert consensus was established by achieving at least 75% agreement and a d-value (d-construct) threshold of ≤0.2, per the accepted FDM criteria [18]. A defuzzification process was then conducted to rank the importance of each item based on expert scoring. These procedures enhanced the scientific credibility and contextual relevance of the final training content, which was structured around three primary learning domains: ergonomic knowledge, self-prevention, and self-evaluation. The proposed items were compiled into a module guided by these expert-reviewed constructs.

ARPE Training Module Platform Selection

The AR was developed in the MAKAR XR platform, chosen for its user-friendly interface, cross-platform support, cost-effectiveness, and proven utility in educational and training settings [19]. MAKAR XR enables the creation of AR, VR, and mixed reality (MR) content on iOS, Android, and web, allowing educators and developers to design immersive simulations without complex coding. The ARPE module featured scenario-based simulations with 3D models showing proper MMH, body posture, and ergonomic tool use. Users interact with digital objects, receive audiovisual feedback, and refine ergonomic practices in realistic settings. The module was optimized for mobile, with an intuitive interface to boost engagement and learning. The instructional designer was a certified professional technologist with expertise in instructional design, ergonomics, and AR training systems. The platform was chosen independently based on research needs, with no influence from financial or institutional interests.

Assessment Tool Development and Validation

To evaluate the ARPE module, we developed a multi-domain assessment battery that covers ergonomic knowledge (primary) and self-prevention and self-evaluation (secondary). The knowledge test was aligned with occupational ergonomics guidelines and translated into Malay (scored 0-100%). The behavioral instruments were adapted from Diego-Mas et al. and operationalized through PQ (Perceived Risk; 11 items: Concern, Control, Loads, Repetitiveness, Postures), RQ (Reaction; 6 items: Prior AR Exposure, Expectation, Interest, Usefulness), and SA (Self-Assessment; 7 items: Memory, Concern, Control), all using 7-point Likert scales with domain scores calculated as item means (higher scores indicate a greater presence of the construct) [14]. Translation and cultural adaptation were followed by assessments of content validity (Content Validity Index (CVI); 7 experts), face validity (Face Validity Index (FVI); 10 MMH workers), construct validity (Exploratory Factor Analysis (EFA); n=100), and reliability testing. For CVI, we applied standard acceptability criteria (Item-level Content Validity Index (I-CVI) ≥0.78; Scale-level Content Validity Index, average method (S-CVI/Ave) ≥0.90), consistent with recommended procedures in content validity studies [20]. For factorability, we required Kaiser-Meyer-Olkin (KMO) >0.60 and Bartlett's test p<0.05, with primary loadings ≥0.40. Internal consistency was considered acceptable at Cronbach's α ≥0.70, good at ≥0.80, and excellent at ≥0.90 (with corrected item-total correlations ≥0.30). Test-retest reliability was assessed using the intraclass correlation coefficient (ICC) (two-way, absolute agreement), with the following thresholds: <0.50 poor, 0.50-0.74 moderate, 0.75-0.89 good, and ≥0.90 excellent. 95% confidence intervals (CIs), standard error of measurement (SEM), and minimal detectable change at the 95% confidence level (MDC_95) will also be reported. In prior related studies, the scales demonstrated α coefficients ranging from 0.71 to 0.92 [14]. All analyses will be performed using IBM SPSS Statistics for Windows, Version 29.0 (IBM Corp., Armonk, New York, United States).

Phase 1b: usability outcome (ARPE (AR) mobile app usability)

Usability will be evaluated using the Malay version of the Mobile Health App Usability Questionnaire (M-MAUQ) [21]; its conceptual framework and item pool are grounded in the original English MAUQ development and validation by Zhou et al. [22]. The 18-item instrument includes three domains, namely, ease of use (5 items), interface satisfaction (7 items), and usefulness (6 items), rated on a 7-point Likert scale (1 (strongly disagree) to 7 (strongly agree)). Acceptable usability is defined beforehand as a mean item score above 4.0 (i.e., above the neutral midpoint), which corresponds to a total score of 72 or higher out of 126 (18×4). This threshold indicates a clear tendency toward positive usability on a 7-point scale and is commonly used for MAUQ-based app evaluations when no specific clinical cut-points are available. For better understanding, we will also report categories at the domain level: minimal acceptable (>4.0 to <5.0), good (≥5.0 to <6.0), and excellent (≥6.0). Phase 1b will use a cross-sectional, post-use design with an independent sample of approximately 100 MMH workers. Participants will receive a brief orientation and a guided first use of the ARPE app and then complete the M-MAUQ immediately afterward in the same session. Regarding feedback, we will calculate mean scores for each domain and item; any item with a mean score of 4.0 or less, a corrected item-total correlation below 0.30, or recurring free-text concerns will be flagged for revision. Results will be compiled into an action log (UI issues, content clarity, navigation), prioritized by severity and frequency, and addressed quickly before starting the Phase 2 quasi-experimental study. Reliability (Cronbach's α; optional test-retest ICC in a subsample) will be reported according to the thresholds specified in the Assessment Tool Development and Validation subsection.

Phase 2: evaluation of the AR ergonomic training module's effectiveness

This Phase 2 evaluation employs a two-arm, parallel-group, quasi-experimental design among warehouse MMH workers. To minimize cross-group contamination at the worksite, allocation is non-randomized at the site level to (i) ARPE training (intervention) or (ii) standard guideline-based training (control) in approximately a 1:1 ratio. We will report baseline comparability between groups in terms of demographics, job tenure, department/shift, prior ergonomic training, and baseline outcomes. Any imbalances will be addressed analytically.

Eligibility Criteria

This study will involve Malaysian citizens employed as MMH workers in warehouses. Participants shall be at least 18 years old and regularly engage in MMH tasks such as lifting, lowering, pushing, pulling, carrying, holding, or restraining objects that exceed 14 kilograms, according to the National Institute for Occupational Safety and Health (NIOSH) guidelines 2015. They must work at least eight hours daily and perform these tasks as part of their routine responsibilities. Additionally, participants must have a mobile phone capable of downloading and using the MAKAR XR app. Those excluded from participation include pregnant individuals, anyone who has attended ergonomic training within the past six months, and interns or temporary workers.

Setting and Recruitment

The study takes place at two warehouses in the Klang Valley. We recognize differences between sites, such as task variety, shift schedules, and prior ergonomic training, which could influence the results. Recruitment is coordinated with each company's safety and health committee through invitation emails and letters, workplace posters, e-posters in departmental WhatsApp groups, and targeted phone calls. Interested workers are screened based on specific inclusion and exclusion criteria and are asked to provide their consent individually.

Allocation

To reduce cross-group contamination, allocation is non-randomized at the site/shift level: one warehouse is assigned to ARPE (intervention) and the other to guideline-based training (control). The site closer to HQ was pragmatically chosen for the intervention to ease monitoring; the second site serves as the control. The sites are geographically separated to minimize contact between groups. We acknowledge that differences between sites may confound the results; therefore, we will (i) document site characteristics (department mix, average load profiles, previous musculoskeletal disorder (MSD) initiatives), (ii) report baseline comparability using standardized mean differences (SMDs), and (iii) adjust analyses as described below.

Sample Size

The sample size was determined from a previous study, which indicated a 57.5% improvement in knowledge [23]. In this study, 52.5% of participants demonstrated very good self-efficacy, while 85% reported perfect practice following the ergonomic training program (ETP) in the experimental group. This calculation utilized a 95% CI and an 80% power. The calculated sample size required was 28 participants per group. To account for a 40% attrition rate [24], an additional 11 participants were included, resulting in a final sample size of 39 participants per group informed by reports of high turnover in shift-based workforces [24]. Therefore, the total number of participants required for this study is 78, ensuring sufficient power to detect significant differences between the intervention and control groups while accounting for potential participant dropout.

Intervention

The study aims to enhance workers' understanding of ergonomics, increase awareness of WMSDs, promote a culture of workplace safety and health, and encourage the adoption of effective ergonomic practices. The ARPE module is based on scientific evidence, including literature, manuals, and guidelines aligned with the Department of Occupational Safety and Health (DOSH) for MMH workers. Its structure, which includes three domains and 25 subdomains, is summarized in Table 1. Operational steps are shown in Figure 1: eligibility screening and recruitment by warehouse; non-randomized, site-level assignment (Warehouse A: ARPE; Warehouse B: conventional training); baseline assessment at week 0; immediate post-knowledge assessment at week 1; and a follow-up evaluation at week 6 across all three domains, with withdrawals/losses to follow-up recorded. Participants in the intervention and control groups were recruited from separate warehouses to minimize cross-contamination, and subsequent statistical analyses were conducted as outlined in Figure 1.

**Table 1 TAB1:** Domains, variables, instruments/tools, timepoints, and purposes of assessment in the ARPE study t_0_: baseline (pre-intervention); t_1_: week 1 (post-knowledge evaluation); t_2_: week 6 (final follow-up) PQ: Perceived Risk; RQ: Reaction; SA: Self-Assessment; ARPE: Augmented Reality Physical Ergonomics

Domain	Variable	Instrument/tool	Timepoints	Purpose
Baseline characteristics	Age, gender, ethnicity, education level, job category, years of service, shift work, work process	Self-administered questionnaire (Malay version)	t_0 _ (week 0: before intervention)	To describe participant demographics and work-related characteristics
Primary outcome	Ergonomic knowledge	Adapted Diego-Mas et al.'s PQ Questionnaire [14]	t_0_, t_1_,t_2_	To evaluate knowledge acquisition and the retention of ergonomic principles
Secondary outcome 1	Self-prevention	Adapted Diego-Mas et al.'s PQ Questionnaire [14]	t_0_, t_1_, t_2_	To assess the implementation of preventive ergonomic behaviors
Secondary outcome 2	Self-evaluation	Adapted Diego-Mas et al.'s RQ and SA Questionnaires [14]	t_0_, t_1_, t_2_	To assess awareness and self-assessment of ergonomic risks and practices

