## Results

Planned outcomes and data analysis

Since this is a protocol, no results are available yet. The primary outcome is ergonomic knowledge, while secondary outcomes include self-prevention behaviors and self-evaluation, measured at baseline (T0), post-training (T1), and six weeks later (T2). Analyses will follow intention-to-treat principles using repeated-measures mixed models (fixed effects: group, time, group×time), with site effects and adjustments for baseline scores and prespecified covariates (e.g., age, tenure, department/shift, prior training). Two-sided α=0.05; results will be reported as adjusted mean differences with 95% CI. Sensitivity analyses will incorporate site-clustered standard errors (SEs), a random intercept for the site if applicable, and inverse-probability-of-treatment weighting. Outcome assessors and the statistician will remain blinded to group allocation. 

Protocol Status and Timeline

Recruitment and baseline assessments are ongoing; follow-up continues through November 2025, after which data will be cleaned and analyzed. No interim results are available.

Interpretation of Change

A structured outcome framework was created to assess the effectiveness of the ARPE training module. The assessments are divided into three domains: ergonomic knowledge (the primary outcome), self-prevention behaviors (secondary outcome 1), and self-evaluation skills (secondary outcome 2). Each domain is evaluated at three key timepoints: baseline (t_0_, before the intervention), week 1 (t1, after the intervention to assess knowledge), and week 6 (t2, follow-up post-intervention). The tools used are adapted from Diego-Mas et al. [14]. All scales are scored so that higher scores reflect better outcomes. The primary endpoint is the change in ergonomic knowledge from baseline to immediate post-training (T0→T1). ARPE will be considered superior if the adjusted group-time effect (ARPE-control) is positive with a 95% CI that does not include 0 (two-sided α=0.05); persistence will be evaluated at T2. For secondary domains (self-prevention, self-evaluation), adjusted group×time effects at T1 and T2 will be regarded as improvements when the 95% CI excludes 0; these analyses are exploratory and supportive.

Baseline Characteristics

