Self-prevention (PQ-derived domain mean; 7-point Likert scale; higher scores indicate better performance; scores are rescaled from 0 to 100) will be analyzed using GEE (identity link, Gaussian), clustering on participants with robust (sandwich) SEs and an exchangeable working correlation. The model includes group (ARPE vs. control), time (t_0_, t_1_, t_2_), group×time, site (fixed effect), and prespecified covariates (age, tenure, department/shift, prior training). Between-group change is tested via group×time with prespecified contrasts reporting marginal ARPE-control differences at t_1_ and t_2_ with 95% CI (two-sided α=0.05) and SMDs. Within-group change (t_1_-t_0_, t_2_-t_0_) will be presented using model-based marginal contrasts (descriptive). Missing data will be addressed under MCAR/MAR using GEE with robust SEs; sensitivity analyses will include inverse-probability-weighted GEE.

Secondary Outcome 2: Self-Evaluation 

Self-evaluation will be assessed using adapted RQ and SA domain means (7-point Likert scale; higher scores indicate better performance; scores are rescaled from 0 to 100). Repeated measures (t_0_, t_1_, t_2_) will be analyzed with GEE using an identity link and Gaussian family, clustering on participants with robust (sandwich) SEs and an exchangeable working correlation (Quasi-likelihood under the Independence model Criterion (for comparing GEE correlation structures) (QIC) to compare AR(1) and unstructured). The model includes group (ARPE vs. control), time, the interaction between group and time, site (fixed effect), and prespecified covariates (age, tenure, department/shift, and prior training). Between-group differences will be tested via the group×time interaction, with prespecified contrasts reporting marginal ARPE-control differences at t_1_ and t_2_ (95% CI; two-sided α=0.05; SMDs shown). Within-group changes (t_1_-t_0_, t_2_-t_0_) will be derived from model-based marginal contrasts (95% CI) and presented descriptively; inference will follow the GEE model.

Data Collection

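### The self-evaluation outcome takes in the RQ, which includes prior AR exposure, so ARPE can gain on it from app use rather than from better self-assessment

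*Protocol article*

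**What the plan says.** The section Assessment Tool Development and Validation names two instruments that later serve self-evaluation: "RQ (Reaction; 6 items: Prior AR Exposure, Expectation, Interest, Usefulness" and "SA (Self-Assessment; 7 items: Memory, Concern, Control". Both use 7-point items, with "domain scores calculated as item means (higher scores indicate a greater presence of the construct". No item is set aside.

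Table 1 assigns the "RQ and SA Questionnaires" to secondary outcome 2 at t0, t1 and t2, and gives its purpose as "To assess awareness and self-assessment of ergonomic risks and practices".

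The section Secondary Outcome 2: Self-Evaluation says "Self-evaluation will be assessed using adapted RQ and SA domain means (7-point Likert scale; higher scores indicate better performance", adds that "scores are rescaled from 0 to 100", and tests the group×time interaction with ARPE-minus-control contrasts at t1 and t2. Interpretation of Change states that "All scales are scored so that higher scores reflect better outcomes", without exception. It counts a secondary effect as an improvement when its 95% CI excludes 0, and calls the secondary analyses exploratory and supportive.

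Under Intervention, the ARPE group downloads the AR app and is expected to view the module within two to three days. The control group has a briefing and lectures, and no AR is described for it.

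**The concern.** Taken together, these statements score more AR exposure as better self-evaluation and measure it again after only one arm has been given AR. That part of the score can move because of allocation itself, with no change in anyone's ability to recognise or judge ergonomic risk. It also does not match the purpose that Table 1 gives for the outcome.

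Nothing planned in the analysis would remove such a shift. Covariate adjustment, site effects, weighting and blinded analysis deal with differences between workers or sites, or with analyst bias, and false-discovery-rate control deals with chance findings. Here the problem is in the definition of the outcome. At stake is whether a positive self-evaluation result can be read as a training effect. Self-evaluation is one of the three outcomes named in the Abstract.

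**Working it through.** The protocol gives no figure on this point, so there is none to reproduce. The check asks how far the score can move through the exposure content alone.

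**Inputs from the protocol:** RQ has 6 items and SA has 7, so 13 in all; each is scored 1 to 7; domain scores are item means; scores are rescaled to 0-100.

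**Assumptions:** rescaling is linear, (x − 1)/6 × 100. Let k be the number of exposure items (not given; k = 1 below) and p the rise per item in Likert points, in ARPE only. Nothing else changes.

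**Formulas for the shift on the 0-100 scale**
- 13 items pooled: 100 × (k·p/13)/6
- RQ and SA means averaged: 100 × (k·p/6)/2/6
- RQ analysed alone: 100 × (k·p/6)/6

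**Results for k = 1**

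| Rise p | 13-item mean | Average of RQ and SA means | RQ alone |
|---|---|---|---|
| 1 | 1.3 | 1.4 | 2.8 |
| 3 | 3.8 | 4.2 | 8.3 |
| 6 (1 to 7, the ceiling) | 7.7 | 8.3 | 16.7 |

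For example, p = 6 pooled gives 6/13 = 0.46 raw points, and 0.46/6 × 100 = 7.7. With k = 2 or 3 the entries double or triple.

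**Could such a shift alone produce a CI that excludes 0?** The protocol gives no SD for this score, so 10, 15 and 20 are assumed. The approximation is a plain two-group comparison of means with 28 per group (the stated number before the attrition allowance), two-sided α = 0.05. It does not reproduce the planned GEE.

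| Shift | SD 10 | SD 15 | SD 20 |
|---|---|---|---|
| 4.2 | 0.34 | 0.18 | 0.12 |
| 8.3 | 0.88 | 0.55 | 0.34 |
| 16.7 (RQ alone) | about 1.00 | 0.99 | 0.88 |

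**Other RQ content.** If the five remaining RQ items (k = 1) also refer to AR and each rose by 1 point in ARPE only, the further shift would be 100 × (5/13)/6 = 6.4 pooled, or 100 × (5/6)/2/6 = 6.9 averaged. This is conditional, because the wording is not shown.

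**The case against.** The strongest reply is that everything turns on item wording, which the article does not give. The word Prior may point to AR use before the study. Such an item would stay roughly constant from t0 to t2 and add little or nothing to the contrast. This limits the size. It does not rescue the scoring, since a fixed fact about a worker's past has no place in a repeated score where higher means better.

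Second, the AR briefing and app download fall in the same session as the baseline assessment, so some exposure may already be in the t0 score and reduce the measured change. That stands, and the order of events within the session is not stated.

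Third, the text speaks of domain means in the plural and never says that RQ and SA are pooled. If they are analysed separately, the SA contrast is clean and already planned, and the problem is confined to an RQ result presented as self-evaluation. That also stands, and it is why the RQ-alone figures are shown next to the two composites.

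A reader might go further and infer that exposure scores must rise in ARPE, so that the contrast is certainly biased, or that control workers' usefulness answers concern a technology they never saw. The document does not support either. Expectation, Interest and Usefulness could refer to whichever training was received, the instruments are described as adapted, and nothing fixes the direction in which those answers would move.

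**Conclusion.** The point holds as a defect in a stated scoring rule. The RQ, with its Prior AR Exposure content, forms part of a self-evaluation outcome on which higher is better, and no section removes that content or restricts it to baseline. ARPE can therefore be credited with a gain that reflects use of the app.

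If one exposure item rises by 1 to 6 points in ARPE only, the artefact is 1.3 to 8.3 points on the 0-100 scale when RQ and SA are combined, and 2.8 to 16.7 when RQ is analysed alone. The upper ends require every ARPE worker to move from 1 to 7 and no control worker to move, so they are ceilings and not expected values. The shift is smaller or nil if the item covers only AR use before the study, or if the exposure is already in the baseline score. A similar problem with the other RQ content is possible but not shown.

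The consequence is bounded: the outcome is secondary, its analysis is labelled exploratory and supportive, and the primary endpoint (change in ergonomic knowledge from t0 to t1) is unaffected. The change should be made, but it does not threaten the main conclusion of the trial.

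**What to change.** - In Table 1 and in Secondary Outcome 2: Self-Evaluation, base the between-arm self-evaluation contrast on the SA domain mean (7 items), scored the same way at t0, t1 and t2.
- Take Prior AR Exposure out of the self-evaluation score. Use its t0 value as a baseline characteristic or covariate.
- Report the RQ separately as reaction to training, not as self-evaluation performance.
- Limit the statement in Interpretation of Change that higher is better on every scale, so that it no longer covers AR exposure.

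SA is already collected, so no new data are needed. Protocol Status and Timeline says that no interim results are available, so the change can still be made without knowledge of the results, provided it is fixed before analysis. The costs are a shorter scale, which may be somewhat less reliable, and a protocol amendment, which goes to the Research Ethics Committee if judged substantial.
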